	Time-to-imaging decision	Compare time from triage to CT decision between arms.	Evaluate whether biomarker access accelerates or delays decision-making.
	Disposition flow	Evaluate differences in ED-to-disposition pathways with vs. without biomarker data.	ED throughput times, floor/ICU admissions.
Secondary (validation) full cohort as single arm	Diagnostic accuracy	Determine sensitivity, specificity, NPV, and PPV of biomarkers vs. CT findings for intracranial lesions.	Biomarker levels vs. CT results.
	Kinetic profiling	Evaluate the kinetics and temporal profile of GFAP/UCH-L1 across 0, 8, 16, and 24 h.	Serial biomarker levels, time-to-peak and decay curves.
	Predictive modeling	Build multivariable models using biomarkers and clinical data to predict imaging-positive patients.	ROC curves, AUC, logistic regression outputs.
	Triage integration	Assess biomarker utility in supplementing current BIG criteria for TBI triage.	Sensitivity/specificity when combined with BIG criteria.
	Outcome prediction	Evaluate whether biomarker levels predict functional outcomes or neurologic decline.	Correlation with GOSE score, readmission, or symptom progression.
Secondary (implementation) only published cohort	Implementation feasibility	Assess provider adherence to biomarker interpretation guidelines in the biomarker-published arm.	Understand clinical adoption barriers and fidelity to protocol including provider and patient variables
	Patient perception	Evaluate patient understanding and satisfaction with biomarker-driven decision-making.	Gain insights into trust and acceptance of non-imaging diagnostics.

TBI, traumatic brain injury; CT, computed tomography; ED, emergency department; LOS, length of stay; ICEA, incremental cost-effectiveness analysis; GCS, Glasgow Coma Scale; GOS, Glasgow Outcome Scale; GOSE, Glasgow Outcome Scale-Extended; ICU, intensive care unit; NPV, Negative predictive value; PPV, Positive predictive value; ROC, Receiver Operating Characteristic; AUC, Area under the curve; BIG, Brain Injury Guidelines.

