### Pre-randomization procedures

Screening of eligible patients will be performed by study personnel via real-time tracking of ED dashboard for new admissions or transfers. Triage notes and evaluations will be reviewed for primary eligibility based on age, type of injury, reported GCS, timing of injury and whether existing head imaging is present. If subjects pass screening, they will be approached for review of detailed inclusion and exclusion criteria and for consent process. Written informed consent (from the patient or legally authorized representative) is obtained before any study-specific activities. Providers are notified about patient enrollment and requested to hold off on obtaining CT head imaging until randomization and biomarker data is available. Randomization variables will then be obtained, and subjects will be randomized using an automated algorithm implemented in RedCap into published or blinded biomarker groups.

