### Post-randomization in-hospital assessment

After allocation, participants are followed throughout their ED stay and – if admitted– for the duration of hospitalization. Study coordinators prospectively capture whether a head-CT is performed, its timing and radiology results; emergency-department and inpatient length of stay; any neurological deterioration or other adverse events; and final disposition or admission status.

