### Safety analysis

Safety analysis will be evaluated by assessing the rate of delayed diagnosis of significant intracranial findings that require intervention and will be compared between the two groups using a Pearson’s Chi-squared test. The time to CT head imaging will also be compared between two groups using a two-sample *t*-test or Wilcoxon rank sum test depending on the normality assumption.

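### The time-to-imaging-decision outcome starts at triage and so includes time before randomisation, which can cost precision but causes no bias; the only listed timing tests use the scan, not the decision

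*Protocol article*

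**What the plan says.** In Table 2, the row Time-to-imaging decision sets out to "Compare time from triage to CT decision between arms", and its stated purpose is to "Evaluate whether biomarker access accelerates or delays decision-making". The start is triage and the event is the decision. A separate row, Clinical decision-making, has CT timing and provider rationale as its outcome.

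Pre-randomization procedures gives the order of events:
- "Triage notes and evaluations will be reviewed for primary eligibility based on age, type of injury", among other items.
- "Written informed consent (from the patient or legally authorized representative) is obtained before any study-specific activities".
- Providers are told of the enrolment.
- "Randomization variables will then be obtained, and subjects will be randomized using an automated algorithm".

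On data capture, Post-randomization in-hospital assessment says: "Study coordinators prospectively capture whether a head-CT is performed, its timing and radiology results". It does not mention the time of the order or of the decision.

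On analysis, Safety analysis says: "The time to CT head imaging will also be compared between two groups", by t-test or Wilcoxon test. Secondary analyses restates the physician decision-making objective and names time to obtaining the head CT, by t-test, as its measure. Neither section states a start point or a covariate for the timing comparison.

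**The concern.** The row asks whether seeing the biomarker result speeds up or slows down the decision. Only time after randomisation can carry that effect. Time spent on screening, consent and set-up has the same expected length in both arms. It can add spread to the outcome, and it tells us nothing about the intervention.

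The event is the second problem. A decision and a scan are different moments, because any wait for the scanner and transport lie between them. If physician decision-making is judged by scan time, those steps are counted as part of the decision.

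At stake is the reading of a null result. An imprecise comparison that shows no difference could be reported as evidence that the test causes no delay.

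**Working it through.** **Does the interval contain pre-randomisation time?** Yes. Triage notes are used to screen, consent follows screening, and randomisation follows consent. Write the outcome as Y = X + P, where X is triage to randomisation and P is randomisation to decision. The arm can affect P but not X.

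**Bias.** X is fixed before allocation, so its expected value is the same in both arms. The difference in mean Y therefore estimates the difference in mean P. There is no bias.

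**Precision.** The article gives no SD, target difference or power for this outcome, so there is no figure of the plan to reproduce. The inputs are:
- 150 evaluable patients per arm, from Sample size justification. That section sizes the CT proportion; I use only its count.
- Two-sided 5% level, from Primary efficacy analysis.
- A difference of 15 min, for illustration. This is the approximate assay delay given under Procedures for the published biomarker arm, not a target effect.
- SD of P 30 min, and SD of X 15, 30, 60 or 120 min. These are assumptions.
- X and P independent. This is also an assumption.

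Total SD = √(SD_X² + SD_P²); SE = total SD × √(2/150); power = Φ(15/SE − 1.96).

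| SD of X (min) | Total SD (min) | SE (min) | 15/SE − 1.96 | Power |
|---|---|---|---|---|
| 0 (clock from randomisation) | 30.0 | 3.46 | 2.37 | 99% |
| 15 | 33.5 | 3.87 | 1.91 | 97% |
| 30 | 42.4 | 4.90 | 1.10 | 86% |
| 60 | 67.1 | 7.75 | −0.02 | 49% |
| 120 | 123.7 | 14.28 | −0.91 | 18% |

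Power of 80% needs a total SD of at most about 46 min.

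**Sensitivity to the assumptions.**
- If the SD of P is 60 min, power is only 58% even with the clock started at randomisation. The triage start is then not the main difficulty.
- With correlation ρ between X and P, the total variance is SD_X² + SD_P² + 2ρ·SD_X·SD_P. With both SDs 30 and ρ = −0.5 this is 900 + 900 − 900 = 900, so the total SD is 30 and nothing is lost.

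**Adjustment for X.** In a linear model for Y with X as a covariate, the residual SD is SD_P × √(1 − ρ²). This is never larger than SD_P, and it is never larger than the unadjusted SD of Y. Apart from one degree of freedom, adjustment therefore does not lose precision, whatever ρ is. In every row of the table it brings power back to about 99%.

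**Decision against scan.** Set side by side, Table 2 names the decision as the event, the capture section records scan timing, and both listed timing tests use time to the scan. No listed test uses time to the decision.

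**The case against.** The strongest reply has five parts.

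1. *The rows are separate.* The scan-time test in Secondary analyses belongs to the Clinical decision-making row, whose own outcome is CT timing. A reader might infer that the triage-to-decision outcome is analysed as triage to scan. The article does not say so: the tests give no start point and are not tied to that row. An article may also leave that row's test to the analysis plan, so its absence is no fault. This stands. What remains is that the article measures physician decision-making by the scan.

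2. *The loss may be small.* A reader might infer that waiting time swamps the effect. No SD or waiting time is given, and at a pre-randomisation SD of 15 min the loss is about two percentage points. This stands; the claim can only be that precision may suffer.

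3. *Fifteen minutes is not an effect of interest.* It is the assay delay, and the objective looks in both directions without a size. The request to hold CT is worded for enrolled patients generally, while the blinded-arm section asks nothing further of providers. How much of the delay differs by arm is therefore unclear. This stands, so 15 min serves only as a scale.

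4. *Triage to decision is a meaningful emergency-department interval.* It is. Covariate adjustment keeps it as the outcome.

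5. *Starting at randomisation is not clean.* Providers are asked to hold off obtaining the scan, which does not prevent an order before randomisation, so the interval could be negative. This stands, and it favours adjustment over moving the clock.

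**Conclusion.** The point holds in a limited form. The outcome as defined includes time before allocation, and the timing tests that are listed are unadjusted and use the scan. The comparison is unbiased; only the precision of one unpowered secondary outcome is affected.

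The size depends wholly on assumed SDs and on independence of the two parts of the interval. With a post-randomisation SD of 30 min, the loss runs from trivial (99% to 97%) to about half the power (99% to 49%) as the pre-randomisation SD goes from 15 to 60 min.

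Power figures restricted to scanned patients would look worse. On the plan's rates, with the 15% reduction read as absolute, these are 0.70 × 150 = 105 against 0.55 × 150 = 82.5 patients. Power is then about 92% from randomisation, against 67% or 33% for a pre-randomisation SD of 30 or 60 min. Those figures do not fit this outcome, because a decision to scan or not to scan can be timed for everyone. That scan time exists only for scanned patients, a group which the arm itself influences, is a separate matter.

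This is a worthwhile refinement, not a threat to the trial's conclusions.

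**What to change.** Keep triage to CT decision as the outcome, and analyse it with the triage-to-randomisation interval as a covariate. Alternatively, start the clock at randomisation and state in advance how orders placed before randomisation are handled. Adjustment is the simpler choice, because it keeps the outcome and copes with early orders.

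Define the event as the time of the CT order, or of the decision not to scan, so that every patient contributes. Report time to scan separately, with its start point stated. Align the wording of Table 2, Post-randomization in-hospital assessment, Safety analysis and Secondary analyses. Report the difference with its confidence interval, so that an imprecise null is not read as no delay.

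Cost: triage and randomisation times should already be on record, although the article does not say so. Order or decision times must be extracted in addition to the scan times already captured. For patients who are not scanned, the protocol needs a working definition of when the decision was made. No change to sample size or conduct is needed.

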### Procedures for the published biomarker arm

For the published arm, providers are requested to pause imaging orders until biomarker data is available which requires around 15 min delay. When biomarker data is available, these are printed and provided timely to the provider along with the cut-off for an elevated test. The cut-off used are 65 pg./mL for GFAP and 360 pg./mL for UCH-L1. The provider will also be handed a refresher education on the published data on the negative predictive value (NPV) and positive predictive value (PPV) of the test. The decision whether to pursue a CT of the head will be left to the provider and patient discussion considering the biomarker data. A test is considered non-elevated only if both biomarkers were below the pre-defined cut-off.

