### Post-discharge follow-up

Study staff will conduct structured telephone interviews at 6 months and 12 months after the ED visit to ascertain persistent or late-presenting neurologic symptoms, unplanned healthcare utilization (ED visits, hospital readmissions, outpatient imaging), and any delayed diagnoses of intracranial injury. Future contact is approved by subjects at the time of consent. When participants cannot be reached after three call attempts, electronic health-record review and contact of designated surrogates are attempted to complete the data set. Designated surrogates are individuals determined by the subject to be their emergency contact for the study for future contact and are named at the time of informed consent.

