### Secondary analyses

Relevant secondary analyses reported in Table 2 will be studies as described below:

Assess the impact of biomarker result access on physician decision-making for CT use (Time to obtaining CT head, *t*-test).Hospital Length of stay in published versus blinded group (*t*-test).Hospital costs for published versus blinded group (Incremental cost effectiveness analysis).GCS and GOS-E comparison in published versus blinded groups at 6 and 12 months (Ordinal logistic regressions).Compare rates of discharge, floor admission, and ICU admission between the published and blinded groups (logistic regression for each outcome, taking admission GCS and age as covariates).Within all patients, define the sensitivity and specificity for predicting GOS-E scores at 6 and 12 months for biomarker test as well as when combined with clinical variables and BIG criteria (ROC analysis).Within the published group, study predictors of adherence to biomarker-based guidelines among providers (logistic regression).

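### Biomarker prediction of GOS-E, readmission and symptoms pools both arms with no account of arm, so it can mix prognosis with an effect of disclosure

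*Protocol article*

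**What the plan says.** Table 2 (Study objective) assigns a population to each block of secondary objectives: two-arm comparison, full cohort, or published cohort only. Outcome prediction sits in the block headed "Secondary (validation) full cohort as single arm". Its objective is to "Evaluate whether biomarker levels predict functional outcomes or neurologic decline", and its measure is "Correlation with GOSE score, readmission, or symptom progression".

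The Secondary analyses section carries this forward for GOS-E only: "Within all patients, define the sensitivity and specificity for predicting GOS-E scores at 6 and 12 months for biomarker test", alone and combined with clinical variables and BIG criteria, by ROC analysis. Neither place mentions arm.

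Under Procedures for the published biomarker arm, the results reach the treating clinician: "these are printed and provided timely to the provider along with the cut-off for an elevated test". The CT decision then "will be left to the provider and patient discussion considering the biomarker data". In the blinded arm the results are withheld from clinicians. Post-discharge follow-up uses telephone interviews at 6 and 12 months to "ascertain persistent or late-presenting neurologic symptoms, unplanned healthcare utilization (ED visits, hospital readmissions, outpatient imaging", among other things.

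The clinical-impact block of Table 2 compares neurological deterioration, readmissions, GOS-E and neurological symptoms between arms. Secondary analyses gives an ordinal logistic regression for the between-arm GCS and GOS-E comparison.

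**The concern.** In the published arm the predictor is also the content of the intervention. Disclosure acts according to the biomarker value: an elevated and a non-elevated result push imaging, disposition and return advice in different directions. Any effect on later outcomes would therefore make the biomarker-outcome relation differ between arms.

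Randomization does not remove this. It balances patients across arms, but it does not make the relation the same in an arm where the value is acted on and one where it is not. Masked adjudication does not remove it either, because care, and possibly reporting and care-seeking, can change before anyone adjudicates.

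The plan is also in tension with itself. It treats the effect of disclosure on these outcomes as an open question when it compares the arms, then sets arm aside when it pools them. A single pooled AUC would not show whether it reflects prognosis or the consequences of release. This is separate from incomplete CT verification, since these outcomes are sought in everyone, scanned or not.

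**Working it through.** The plan gives no figure for this analysis: no outcome rates, no share elevated, no disclosure effect. There is nothing to reproduce, and every rate below is an assumption made to show scale. Only the 1:1 allocation and the 300 evaluable patients (150 per arm) come from the documents (Study design and methods; Sample size justification).

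**A. No true association.** Assume 65% elevated (195 of 300; 105 not elevated), a 25% risk of poor outcome without disclosure in both groups (odds 1/3), and all 300 followed. Disclosure multiplies the odds by k in elevated published-arm patients and divides them by k in the non-elevated.

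- Published-arm risk = odds/(1 + odds), with odds k/3 or 1/(3k).
- Pooled risk in each biomarker group = mean of the blinded and published risks.
- Pooled OR = ratio of the odds of the two pooled risks.
- SE of log OR = √[1/(195·p₁) + 1/(195·(1−p₁)) + 1/(105·p₀) + 1/(105·(1−p₀))].
- P(significant) = Φ(z − 1.96) + Φ(−z − 1.96), with z = log OR / SE.

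| k | published risks, elevated / not | pooled risks p₁ / p₀ | pooled OR | z | P(significant) |
|---|---|---|---|---|---|
| 1 | 0.250 / 0.250 | 0.250 / 0.250 | 1.00 | 0 | 5% |
| 1.1 | 0.268 / 0.233 | 0.259 / 0.241 | 1.10 | 0.34 | 6% |
| 1.2 | 0.286 / 0.217 | 0.268 / 0.234 | 1.20 | 0.65 | 10% |
| 1.5 | 0.333 / 0.182 | 0.292 / 0.216 | 1.50 | 1.41 | 29% |

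With a 15% baseline risk, k = 1.5 gives 21% instead of 29%. In every row the blinded-arm OR is 1.00.

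**B. A true association.** Assume 60% elevated, with blinded-arm risks of 30% (elevated) and 15% (not). The blinded arm then has OR 2.43 and AUC 0.599. Let disclosure change risks by 20% relative:

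- Down in elevated, up in the others: pooled risks 0.27 and 0.165; OR = (0.27/0.73)/(0.165/0.835) = 1.87; AUC 0.572.
- Up in elevated, down in the others: pooled risks 0.33 and 0.135; OR = (0.33/0.67)/(0.135/0.865) = 3.16; AUC 0.624.
- No disclosure effect: OR 2.43, AUC 0.599, no bias.

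The bias can go either way.

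**C. Precision by arm.** Half the sample widens an interval by √(300/150) = 1.41. For a correlation, the 95% half-width on the Fisher z scale is 1.96/√297 = 0.114 with 300 and 1.96/√147 = 0.162 with 150. On the inputs of A, power for a true OR of 2.0 (risks 40% and 25%) falls from about 73% (SE 0.269) to about 45% (SE 0.380) if only one arm is used.

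**D. What an interaction test can detect.** At k = 1.5 the arm-by-biomarker log OR is ln(2.25) = 0.811. Its variance is 0.156 (blinded arm) + 0.174 (published arm) = 0.330, so SE = 0.575, z = 1.41 and power is about 29%. A non-significant interaction would say little.

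**The case against.** The other side has several fair points.

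- **What patients know.** A reader might infer that published-arm patients are told their result. The article describes handing it to the provider and a shared discussion that considers it; no step formally discloses the level to the patient. Changes in symptom reporting therefore rest on inference. The provider route (imaging, disposition, return advice) does not.
- **What is pooled where.** A reader might take Secondary analyses to pool all three outcomes. It does so for GOS-E only; readmission and symptom progression rest on one Table 2 cell. An unseen analysis plan could add arm as a covariate, and the clinical variables are not listed. That would soften the point, but the article does not merely leave the population open: it fixes the cohort as a single arm.
- **Ascertainment.** Not every outcome depends on self-report. Neurological deterioration is captured prospectively in hospital, adjudicators are masked, and records and surrogates are used when calls fail. There is no specific reason given to expect a large shift in global function at 6 to 12 months.
- **Size.** Large effects are easy to assume. If all non-elevated published-arm patients had doubled odds, a true OR of 1.5 would shrink to 1.04. But a return-for-imaging route acts only on patients newly left unscanned. If the 15% CT reduction is absolute and falls wholly in the 35% non-elevated, that is 0.15/0.35 = 43% of them, and the pooled OR is 1.27. Near-erasure is not supported.
- **Remedy.** Pooling answers a defensible question, prediction across both care pathways, and moving the headline to the blinded arm costs the power shown in working C.

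These points limit the strength and severity of the concern. They do not remove it: the plan pools without regard to arm while treating the effect of arm on the same outcomes as unknown.

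**Conclusion.** The point holds as a minor one on a secondary objective. The pooled outcome-prediction estimate can mix prognosis with a disclosure effect; the documents do not show that it does. Size and direction are unknown, and the bias is nil if disclosure leaves outcomes unchanged. Under the stated assumptions with no true association, small effects (odds factors of 1.1 or 1.2 each way) raise the false-positive rate from 5% to about 6% or 10%; only a large one (1.5 each way) brings it to about 29%. With a true OR of 2.43, a 20% relative effect in opposite directions moves the pooled value to between 1.87 and 3.16.

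Two stronger readings are not supported: that the pooled estimate is certainly biased, and that the full cohort must be given up for the blinded arm. The primary CT comparison and the between-arm outcome comparisons do not depend on this analysis.

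**What to change.** Keep the full cohort. In the Outcome prediction row of Table 2 and in the GOS-E item of Secondary analyses:

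1. Add arm and arm-by-biomarker terms to the outcome-prediction models.
2. Report sensitivity, specificity and ROC/AUC by arm beside any pooled figure.
3. State that the blinded-arm estimate is the one free of disclosure to clinicians, and that the pooled figure describes prediction across both care pathways.
4. Report the arm-specific figures whatever the interaction test shows, given its low power (working D).

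The cost is wording and a little more analysis. Both arms are already tested and followed, so no new data are needed. Arm-specific intervals will be about 1.4 times wider than the pooled one.
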